|-------------------------------------------------------------------------------------------------------------------------------------------------------------------------------------------------------------------------------------------------------------------------------------------------------------------------------------|-----------------------------------------------------------------------------------------------------------------------------------------------------------------------------------------------------------------------------------------------------------------------------------------------------------------------------------------------------------------------------------------------------------------------------------------------------------------------------------------------------------------------------------------------------------------------------------------------------------------------------------------------------------------------------------------------------------------------------------------------------------------------------------------------------------------------------------------------------------------------------------------------------------------------------------------------------------------------------------------------------------------------------------------------------------------------------------------------------------------------------------------------------------------------------------------------------------------------------------------------------------------------------------------------------------------------------------------------------------------------------------------------------------------------------------------------------------------------------------------------------------------------------------------------------------------------------------------------------------------------------------------------------------------------------------------|
|                                                                                                                                                                                                                                                                                                                                     | 
of care workflow). Patients included in the study can choose in which group they want to be. This way they can choose whether they receive outpatient recovery or the regular recovery path (staying one night in hospital). If the preferred group is full, the patient can choose to participate in the other group, or to withdraw from the study. If the patient has no preference, he/she is randomly assigned to either recovery group, or if one group is full, to the group for which 100 patients have not yet been included. Patient preference is recorded in the eCRF and analysed.
                                                                                                                                                                                                                                                                                                                                                                                                                                                                                                                                                                                                                                                                                                                                                                                                                                                                                                                                                                                                                                                                                  |
| At-Home Subject Procedures                                                                                                                                                                                                                                                                                                   |  NOT APPLICABLE

At home, the subjects are expected to wear the Healthdot device for seven days and interact with their caregivers as needed. Patients are expected to fill in a questionnaire at the end of the 7 days at home.
                                                                                                                                                                                                                                                                                                                                                                                                                                                                                                                                                                                                                                                                                                                                                                                                                                                                                                                                                                                                                                                                                                                                                                                                                                                                                                                                                                                                                       |
| Device(s) / Other support (s)

Check each box as appropriate and add a brief description of the device(s)—e.g., fitness tracker, VR goggles, breast pump, electric toothbrush, ELAN, MRI scanner.

Device(s) and/or other support(s) will be described fully in Section 2.1 of the study protocol.
 |  Mock-up (see ICBE FAQ definition):
 Survey/questionnaire (if copyrighted, ensure permission for use): Satisfaction questionnaire to patient and physician.
 Interview/focus group with audio/video taping**:
 Interview/focus group without audio/video taping**:

**see decision flowchart regarding interviews vs QI vs consulting https://share-intra.philips.com/sites/STS20131115093003/ICBE-FAQ/Lists/Photos/interviews%20criteria%20flowchart%20feb2018.pptx
  FDA or CE-approved medical device within intended use:

Philips Intellivue Guardian system already installed at hospital to view data from Healthdot wearable.
  FDA or CE-approved medical device outside intended use:
 FDA or CE-approved non-medical device within intended use:

Gateway for LoRa reception inside hospital
  FDA or CE-approved non-medical device outside intended use:
 In vitro medical device:
 Medical device prototype***: Healthdot
 Non-medical device prototype***:
 Software prototype***, non-medical:
 Software prototype***, medical:
 Other:
 None |
| 
***Before a study employing prototypes may start, a Declaration of Conformity (DoC) needs to be issued by the Director Regulatory Affairs. With this DoC, Philips declares that the
                                                                                                                                          |                                                                                                                                                                                                                                                                                                                                                                                                                                                                                                                                                                                                                                                                                                                                                                                                                                                                                                                                                                                                                                                                                                                                                                                                                                                                                                                                                                                                                                                                                                                                                                                                                                                                                         |

Gewijzigde v

|                                                                                                                                                   |                                                                                                                                                                                                                                                                                                                                                                                                                                                                                                                                                                                                                                                                                                                                                                                                    |
|---------------------------------------------------------------------------------------------------------------------------------------------------|----------------------------------------------------------------------------------------------------------------------------------------------------------------------------------------------------------------------------------------------------------------------------------------------------------------------------------------------------------------------------------------------------------------------------------------------------------------------------------------------------------------------------------------------------------------------------------------------------------------------------------------------------------------------------------------------------------------------------------------------------------------------------------------------------|
|                                                                                                                                                   | 
device can safely be used in the study. It may be needed to work according to some formal standards to build up this evidence (e.g. with respect to bio-compatibility or sterility).
 
***  DoC needed (brief overview of the actions that will be taken to get the Declaration of Conformity. See Philips Research QMS procedure "Procedure Product Release (QR-PRO-36)". Give details of how the project will deal with the regulatory requirements. Consult the Q&R office when needed): A declaration of conformity will be requested from regulatory affairs based on the Design history file and the Investigational Medical device Dossier of the Healthdot.
                                                                             |
| Milestones                                                                                                                                 | 
Study start (first patient first visit): Dec 2020 (planned)
 
Interim analysis (after 50 patients): Mar 2021 (planned)
 
Study end (last patient last visit): Jul 2021 (planned)
 
Final Report: Oct 2021 (planned)
                                                                                                                                                                                                                                                                                                                                                                                                                                                                                                                                                          |
| Claims                                                                                                                                     | 
Will you obtain regulatory (FDA, CE) approval for a new product or service, a new indication, or a new marketing claim?
 
 Yes    No
 
If YES, in what countries will the claims be registered?
 
 Netherlands    USA    Germany    China
 
 India    Belgium    UK    Kenya
 
 Other:
 
Have you developed a list of claims that you would like to assert for your product or service?    Yes    No
 |
| External Medical Ethics Committee Approval

Note: if your document is not in English or Dutch, include an English translation | 
 Not Required (not a local/state/country requirement)
 
 Required (apply for it AFTER ICBE approval)
 
 Approval already obtained (upload for review by ICBE)
 
 REC Review is waived (upload review waiver)
 
 REC has waived requirement for informed consent (upload waiver)
 
 Check this box if more than one REC is involved in this study and identify them:
                                                                                                                                                                                                                                     |
| Submission to Competent Authorities                                                                                                        | 
 Not applicable
 
Check the applicable option concerning Competent Authority approval for medical device studies:
 
 No submission to Competent Authority needed, since no non-released medical device involved
 
 Approval from Competent Authority is mandatory for this study with a non-released medical device
                                                                                                                                                                                                                                                                                                                                                                       |

|                                                              |                                                                                                                                                                                                                                                                                                                                                                                                      |
|--------------------------------------------------------------|------------------------------------------------------------------------------------------------------------------------------------------------------------------------------------------------------------------------------------------------------------------------------------------------------------------------------------------------------------------------------------------------------|
|                                                              | Note: Released medical device means a device that is e.g. CE-marked (93/42/EEC) if study takes place in EU, or has 510k if study takes place in USA.                                                                                                                                                                                                                                                 |
| Database registration                                 |  No
 Yes : ClinicalTrials.gov                                                                                                                                                                                                                                                                                                          |
| Type of Legal Agreement for this study                |  None required  MRA Exhibit
 Contract  Purchase Order                                                                                                                                                                                                                                  |
| Status of Legal Agreement                             |  NA  Not started  In Process  In Place
Name of Legal Representative: [name]                                                                                                                                                                                                    |
| IP Strategy                                           | IP rights of Philips in this project are described in the eMTIC contract and the appended Exhibit specific for this study.                                                                                                                                                                                                                                                                           |
| ICBE Training is required for all key study personnel |  YES, this training is completed as required by ICBE*
 NO, this training is not completed as required by ICBE*:
*See FAQ: https://share-intra.philips.com/sites/STS20131115093003/ICBE-FAQ/Lists/Posts/Post.aspx?ID=159 |

Gewijzigde v

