| Accessories             | Not applicable                                                                                                                                                                                                                                                                                                                                                                                                                                                                                                                                                                                                                                                                       |
| Traceability procedure  | 
The device traceability during and after the clinical investigation is documented in form "Device Accountability". This record is intended to document the physical location of all investigational devices from shipment of investigational devices to the investigation sites until return or disposal.
 
The device is tracked to and from the investigational site by the Study Manager, while the trace to the subjects is done by the Principal Investigator. At clinical investigation termination or closure, device retrieval or disposure will be checked by the Monitor.
 
The devices are uniquely identified by a label containing the serial numbers.
 |
| Required training       | The investigators will be instructed how to handle the Healthdot and where to position it. This will also be described in an instruction for use provided to the investigator. No specific training is required. The patient will be informed on how to act and what to avoid while wearing the device with a separate Patient card.                                                                                                                                                                                                                                                                                                                                                 |

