On day 3-8 the physician will check the Healthdot dashboard daily. The physician may decide to have a telephone consultation, e.g. when the Healthdot dashboard flags an event. If the physician will determine that additional action is needed (e.g. based on the information on the dashboard, or when the patient calls), in the absence of an indication from the Healthdot, such an event will be viewed as a false negative. It will be retrospectively assessed, based on the patient medical record, if false negative events have occurred. For all events flagged in the Healthdot dashboard, the physician will record whether it was a false positive notification or a true positive notification in the eCRF.

Patients in the regular recovery group will be released from hospital on the discretion of a nurse under supervision of the physician the day after surgery. For these patients no appointments outside of the regular protocol are planned.

*Table 1: Overview of protocol activities in the hospital for the two patient groups, and the differences*

| Protocol Activity for patient group
"Outpatient recovery"                                                                                                                                                                                                                                                   | Protocol Activity for patient group
"Regular recovery"                                                                                                                                                                                                                                                      | Differences                                                                                                                                        |

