### ***Follow up***

Patients who received the Healthdot will remove this themselves on day 8. They use a return envelope, which was given to them at discharge, to send back the device to Philips.

Patients in both groups will be requested to fill in a short satisfaction questionnaire on day 8. This questionnaire was given to them at discharge and should be sent to Philips together with the Healthdot device or a provided envelope without the device for the control group. Health care professionals will be requested to fill in a similar satisfaction questionnaire after the entire study is

|                                                                                                                    |              |                        |                  |                    |
|--------------------------------------------------------------------------------------------------------------------|--------------|------------------------|------------------|--------------------|
| Title: Clinical Investigation Plan                                                                                 |              | Author: [name] |                  | Philips restricted |
| DocID: ICBE-2-36455                                                                                                | Version: 3.0 | Date: 2020-DEC-08      | Status: Approved | Page: 28 of 44     |
| This document is based on Philips Research Template: Clinical Investigation Plan, ID: QR-TEM-57, Date: 2019-Mar-21 |              |                        |                  |                    |

completed. The presence or absence of readmission within 30 days will be observed from the patient record.

The questionnaires for the patient and the health care professional can be found in [Table 2](#) and [Table 3](#), respectively.

Met opmaak

Met opmaak

Table 2: Patient satisfaction questionnaire. Patient should circle the selected answer.

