## Missing Data

No replacement of missing data will be performed and the affected measurements will be regarded as lost for final statistical analysis.

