## **11 DEVICE ACCOUNTABILITY**

The procedures for the accountability of investigational devices are in accordance with the Guidance.

|                                                                                                                    |              |                         |                  |                    |
|--------------------------------------------------------------------------------------------------------------------|--------------|-------------------------|------------------|--------------------|
| Title: Clinical Investigation Plan                                                                                 |              | Author: [name] |                  | Philips restricted |
| DocID: ICBE-2-36455                                                                                                | Version: 3.0 | Date: 2020-DEC-08       | Status: Approved | Page: 35 of 44     |
| This document is based on Philips Research Template: Clinical Investigation Plan, ID: QR-TEM-57, Date: 2019-Mar-21 |              |                         |                  |                    |

The access to investigational devices will be controlled and the investigational devices will only be used in the clinical investigation and according to the CIP.

The sponsor shall keep records to document the physical location of all investigational devices from shipment of investigational devices to the investigation sites until return or disposal. This record will be based on device accountability form.

The principal investigator or an authorized designee shall keep records documenting the receipt, use, return and disposal of the investigational devices. This record shall include:

- the date of receipt,
- identification of each investigational device (batch number/serial number or unique code),
- the expiry date, if applicable,
- the date or dates of use,
- subject identification,
- the date on which the investigational device was returned/explanted from subject, if applicable, and
- the date of return of unused, expired or malfunctioning investigational devices, if applicable.

Devices and/or questionnaires will be returned by the patient in a provided envelope to the hospital. The devices will be wiped down with standard alcohol wipes and will be quarantined together with the questionnaire for 4 days at the hospital before return to Philips (Covid-19 measure).

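### The day-8 satisfaction form comes back with the logged Healthdot in one group and alone in an envelope in the other, with no reminder for either, so the secondary satisfaction comparison is open to differential non-response

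*Protocol*

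**What the plan says.** The Executive Summary (At-Home Subject Procedures) announces the form: "Patients are expected to fill in a questionnaire at the end of the 7 days at home". Section 6.4 (Follow up) sets the collection: "Patients in both groups will be requested to fill in a short satisfaction questionnaire on day 8". The form is handed out at discharge and "should be sent to Philips together with the Healthdot device or a provided envelope without the device for the control group".

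The device, unlike the form, is under accountability. Section 2.1 (Traceability procedure) states that "the trace to the subjects is done by the Principal Investigator". Section 11 requires a record that includes the subject and the date of return or removal, and the Schedule of Activities marks device logging on day 8. No corresponding record is described for the form.

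Section 11 gives a different first recipient: "Devices and/or questionnaires will be returned by the patient in a provided envelope to the hospital". There the items are quarantined for four days before going on to Philips.

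After discharge, outpatients have a day-2 teleconsultation and the physician checks their dashboard daily on days 3 to 8 (Section 6.4, Discharge from hospital). For the regular group the same section says: "For these patients no appointments outside of the regular protocol are planned". No reminder about the form is described for either group.

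Section 7 (Missing Data) sets the rule for forms that do not arrive: "No replacement of missing data will be performed and the affected measurements will be regarded as lost for final statistical analysis".

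**The concern.** Two secondary hypotheses in Section 5 rest on this form. One says that the share scoring above 6 out of 10 does not differ significantly between groups. The other says that satisfaction with outpatient recovery is at least as high as with current treatment. Section 7 also lists patient satisfaction among the items compared at the interim analysis, and Section 5 allows claims to be derived from secondary hypotheses.

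In the outpatient group the form travels with an item that has to be sent back and is accounted for. In the regular group nothing but the form itself calls for posting. Return rates could therefore differ. With missing forms dropped, the analysis compares those who answered. If answering also depends on satisfaction, an apparent difference can arise, or a real one can be hidden, without any effect of the recovery path.

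**Working it through.** **No figure of the plan to reproduce.** The protocol gives no expected satisfaction share and no form return rate. Its sample size of 97 per group (100 chosen) belongs to the primary endpoint, and this point does not depend on it.

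**From the protocol:** 100 patients per group; endpoint is the share scoring above 6; missing forms are dropped; the feasibility criterion for missing data is below 10%, not stated by group.

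**Assumed, for illustration only:** a true share p = 85% above 6 in both groups. Outpatients return 95% of forms whatever their score, so their observed share stays at 85%. In the regular group, satisfied patients return a fraction s and dissatisfied patients a fraction d.

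**Formula:** observed share = p·s / (p·s + (1 − p)·d). The denominator is the overall return rate.

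| s | d | Overall return | Observed share, regular group | Shift from 85% |
|---|---|---|---|---|
| 80% | 80% | 0.680 + 0.120 = 80.0% | 85.0% | 0 |
| 92% | 80% | 0.782 + 0.120 = 90.2% | 0.782/0.902 = 86.7% | +1.7 points |
| 70% | 60% | 0.595 + 0.090 = 68.5% | 0.595/0.685 = 86.9% | +1.9 points |
| 60% | 70% | 0.510 + 0.105 = 61.5% | 0.510/0.615 = 82.9% | −2.1 points |
| 80% | 50% | 0.680 + 0.075 = 75.5% | 0.680/0.755 = 90.1% | +5.1 points |
| 60% | 80% | 0.510 + 0.120 = 63.0% | 0.510/0.630 = 81.0% | −4.0 points |

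A positive shift makes outpatients look worse than they are, and a negative one makes them look better. The two largest shifts go with non-return of 24.5% and 37%. The second row, with non-return just under 10%, gives 1.7 points.

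**Sensitivity to p.** At p = 80%, s = 80% and d = 60% give 0.64/0.76 = 84.2% (+4.2 points, 24% non-return). With s = 70% and d = 95% the result is 0.56/0.75 = 74.7% (−5.3 points, 25% non-return). The picture is the same.

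**Against sampling error.** With 95 and 75 returned forms and 85% above 6 in each group, the standard error of the difference is √(0.85·0.15/95 + 0.85·0.15/75) = √(0.00134 + 0.00170) = 0.055, or 5.5 points. The largest shift in the table is below one standard error.

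**Logical limits.** Suppose 90% of returned forms score above 6 in both groups, so the observed difference is zero. Filling in the missing forms in the two most extreme ways bounds the true difference (outpatient minus regular) as follows:
- 95%/95% return: −5 to +5 points.
- 95%/85% return: 0.855 − 0.915 = −6, to 0.905 − 0.765 = +14 points.
- 95%/75% return: 0.855 − 0.925 = −7, to 0.905 − 0.675 = +23 points.

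These are limits, not likely values. They show how unequal return widens what the data cannot rule out.

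**The case against.** The case against runs as follows. Both groups get the same form at discharge, complete it on the same day and post it in a provided envelope. The one difference is that one envelope also holds a device, because only that group wears one. Missing data are an endpoint with a threshold, and leaving missing values unimputed is an ordinary choice. Satisfaction is secondary, and study success rests on the primary endpoint alone. Patients know and mostly choose their group, so self-selection threatens this comparison more than envelopes do.

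Much of this stands, and it limits how far the point can go. A reader might infer four stronger things that the protocol does not support:
- *That regular patients have no contact after discharge.* The sentence rules out only appointments beyond the regular protocol. Table 1 has upcoming appointments explained to both groups, and both may call the hospital.
- *That outpatients are chased and regular patients are not.* Device logging is an accountability record, and the recorded date may be that of removal. Nothing says that a late device prompts a call. The day-2 consultation is clinical and six days before the form is due. The absence of a reminder is the same in both groups.
- *That posting the form to Philips conflicts with keeping contact information at the hospital.* The form in Table 2 shows no name or contact field, and Section 8 lets coded data go to Philips.
- *That the Executive Summary sentence is itself wrong.* It says only that a form is completed. The routes and the missing-data rule are set in Sections 6.4 and 7.

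What remains is that Section 6.4 does fix an unequal return arrangement, and a later analysis plan cannot recover forms that nobody asked for. The missing-data threshold is not by group, so it would not show an imbalance. The conflict over the first recipient is real but applies equally to both groups. It needs a wording fix and is not a source of differential return.

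**Conclusion.** The concern holds as a risk of low severity. Collection is unequal by group, no reminder is described for either, and missing forms drop out, so the secondary satisfaction comparisons are open to differential non-response.

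Size and direction cannot be known from the protocol. The bias is zero if return does not depend on satisfaction. Under mild dependence it is about 2 points or less. It reaches about 4 to 5 points in the scenarios tried only with non-return of roughly 25% to 37% in the regular group. All of this rests on assumed return rates and an assumed true share of 80% to 85%. It would be wrong to conclude that the satisfaction result will be biased, or by how much. Self-selection by preference remains the larger threat to the same comparison, and this change does not remove it. The primary endpoint is unaffected.

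**What to change.** In Section 6.4 (Follow up):
- Name one destination for the form in both groups and reconcile it with Section 11: either Philips directly, or the hospital first with quarantine.
- Log form return for every patient in both groups at the first recipient.
- Give non-returners in both groups the same single reminder around day 8, from a researcher not involved in care.

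The means largely exist. Section 6.3 requires a telephone on which the patient can be reached on days 1 to 8, contact information stays at the hospital (Section 8), and Section 13.1 already describes a researcher who is not directly involved in the surgery or direct care. A reminder a few days after day 8 would fall outside the stated telephone period but could use the same number.

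The cost is protocol wording and a little staff time. Posting the form separately from the device is optional and a trade-off: it would equalise the route but could lower return among outpatients. Best- and worst-case bounds for unreturned forms are also optional and can be left to the analysis plan.
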